### Statistical analysis

Descriptive statistics will be carried out to describe baseline characteristics of intervention and control group to assure comparability between groups.

Intra-group and inter-group FV intake differences at T0, T1, T2 and T3, will be analyzed by Student’s *t* test or non-parametric tests (Wilcoxon signed-rank test and Mann–Whitney U test). The same tests will be carried out to study the evolution of determinants of eating behavior (attitude, subjective norms, perceived behavioral control and intention) at different times.

To understand the relationship between determinants of behavior and behavior itself (FV consumption), multiple linear regression and structural equation modeling (SEM) analysis will be done at different times. Covariance of classic relationship of TPB determinants will be proposed. It will allow us to check the validity of the proposed model, as well as the influence of each determinant on the others and its significance. Changing models will be made by using difference on TPB determinants between different times.

Model validity will be established by comparative fit index (CFI), root mean square-error of approximation (RMSEA) and chi square/degrees of freedom (χ2/df). A good model will be determined by high values of CFI (> 0.90), low values of RMSEA (< 0.10) and χ2/df values from 1 to 3 [35, 36].

Multiple linear regression will be used to study the effect of social demographic variables in the effectiveness of the intervention.

Statistical analyses will be made using STATA 14.0, IBM-SPSS 24.0 and AMOS 24.0 statistical software. IC of 95% and significance level of *p* < 0.05 will be assumed.

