### Sample size

In order to provide a power of 90% to detect an effect size (Cohen’s d) of at least 0.5 servings/day, 172 participants (86 in the intervention group and 86 in the control group) are required. Based in the dropout of similar studies [28–30], the final sample size is increased by 20% to reach 206 children (8 classrooms with a minimum of 26 children per class).

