### Outcomes

#### Primary outcome: Quantitative outcome

FV intake: FV (excluding potatoes and legumes) consumption will be measured by a validated self-fulfilling food record [33]. It provides information about standard servings of FV intake for 7 days, and it must be filled out by parents or legal guardians. To control self-completed food record data reliability, a researcher will make telephonic 24-h dietary recalls (goal-standard) on one randomly chosen day during the week in which the record is being filled.

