#### Secondary outcomes: Qualitative outcomes

Determinants of eating behavior: evolution of determinants proposed (attitude, subjective norms and perceived behavioral control) will be analyzed by a questionnaire designed according to bibliographic proposals [34]. Each determinant will be measured by a minimum of 3 items that will be answered by children marking a number on a 1–5 scale from “totally disagree” to “totally agree”. Validity of the survey will be checked by its internal consistency (Cronbach’s alpha).
Social demographic outcomes and families’ FV consumption habits: data will be collected by a questionnaire designed by the Department of Sociology 2 of the University of the Basque Country to obtain the following information:
Parental educational attainmentParental employment situationTheir perceived importance of their children’s FV intakeTheir level of knowledge concerning FV recommended intakeFV availability and accessibility at homeWhere children have their main mealChildren’s TV watching habits during mealsParents’ FV consumption habits.

Codified surveys will be sent by means of the children inside codified sealed envelopes. These will be filled out at home by parents and returned to school. Questionnaires of behavior determinants of behavior will be completed in 20 min by children at school under the supervision of a nutritionist. All the questionnaires will be completed at the three times described previously (T0, T1, T2) during the academic year and one year after intervention will be finished (T3).

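### The visit-by-visit t or rank tests of fruit and vegetable intake, run on observed records, ignore the earlier records of children lost later; one longitudinal model would use them

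*Protocol article*

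**What the plan says.** - **Analysis** (Statistical analysis): "Intra-group and inter-group FV intake differences at T0, T1, T2 and T3, will be analyzed by Student’s" t test, or by the Wilcoxon signed-rank and Mann–Whitney tests. Regression and structural equation models are also named, but for the behavioural determinants and the sociodemographic variables, not for the between-arm comparison of intake.
- **Outcome** (Primary outcome): intake comes from a 7-day food record, and "it must be filled out by parents or legal guardians".
- **Dropout** (Sample size): "172 participants (86 in the intervention group and 86 in the control group) are required", and then "the final sample size is increased by 20% to reach 206 children". The basis given is the dropout seen in similar studies, with no split by arm or visit.
- **Visits** (Study procedure): T0, T1 and T2 fall within the academic year, and T3 is one year after the programme ends.
- **Contact** (Intervention design): the intervention arm gets 14 one-hour sessions with goal-diaries and worksheets that reach the home. The control arm gets two one-hour lessons.

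**The concern.** A two-sample test at T2 has no term through which a child's T0 or T1 record can enter. A paired test needs both visits. On available records, the T1, T2 and T3 results may therefore rest on different children, and what is already known about a child who later drops out is not used.

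Adding children restores numbers but does not remove bias. If intervention families whose child is eating little stop returning records, and control families do not behave the same way, the intervention mean rises among those who remain and the programme looks better than it is. The opposite pattern would hide a benefit. The T3 comparison is the most exposed, because the Discussion reads it as evidence of lasting adherence, and a change in who still returns a record could be mistaken for maintenance or decay.

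**Working it through.** **1. The plan's own figure.** Inputs from Sample size and Statistical analysis: 90% power, d = 0.5 and alpha 0.05 (two-sided assumed). The effect is labelled both Cohen's d and servings/day, so SD = 1 is assumed. The two-sample t calculation gives 85.03 per arm, hence 86 per arm and 172 in total, which matches. Then 172 × 1.20 = 206.4, which matches 206.

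**2. Loss the plan allows for.** 206 − 172 = 34 children; 34/206 = 16.5%. If 20% were lost, about 165 of 206 would remain and child-level power would be about 89%. Power is therefore not the issue; bias is.

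**3. Formula for the bias.** Let d be the fraction lost in an arm, m the distance in SD by which lost children lie below that arm's T1 mean, and ρ the correlation between visits. If loss depends on T1 intake only, the T2 mean of the retained children is shifted by ρ × d/(1 − d) × m. The bias in the between-arm difference is this quantity in the intervention arm minus the same quantity in control. It is zero when m = 0 in both arms, or when d, m and ρ are alike in both.

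**4. One-arm case, no true effect.** Assumptions, none of them in the document: random loss in control; loss in the intervention arm with a logit slope of 0.5, 1 or 2 per SD of T1 intake; ρ = 0.4 or 0.6; equal correlations between visits.

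| Loss | d/(1 − d) | m for the three slopes | Bias, ρ = 0.4 | Bias, ρ = 0.6 |
|---|---|---|---|---|
| 16.5% | 0.198 | 0.40, 0.73, 1.12 | 0.03, 0.06, 0.09 | 0.05, 0.09, 0.13 |
| 20% | 0.250 | 0.39, 0.69, 1.05 | 0.04, 0.07, 0.10 | 0.06, 0.10, 0.16 |

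Example: 0.6 × 0.198 × 1.12 = 0.13. Simulation with 103 children per arm and 20% loss gives the same values to within 0.01. As shares of the design effect of 0.5, the ranges are about 7% to 27% at 16.5% loss and 8% to 31% at 20% loss.

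**5. Against the standard error.** At 16.5% loss, 86 remain per arm and the child-level standard error is √(2/86) = 0.152, so the bias is about 0.2 to 0.9 of it. Clustering makes the ratio smaller. With an assumed intraclass correlation of 0.05 and 206/8 × 0.835 = 21.5 children per class, the design effect is 1 + 20.5 × 0.05 = 2.03, the standard error 0.217 and the ratio about 0.15 to 0.6.

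**6. Using the earlier records.** Within each arm, T2 was regressed on T0 and T1 among those retained and predicted for all children. The remaining bias was at most 0.005 SD, with no loss of precision. This stands in for the mixed model, which was not itself simulated.

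**7. If loss depends on T2 intake itself.** At 20% loss and the same slopes, the shift among retained children is 0.250 × 0.39, 0.69 or 1.05 = 0.10, 0.17 or 0.26 SD. Using T0 and T1 still leaves 0.07, 0.14 or 0.21 SD (ρ = 0.4) and 0.05, 0.10 or 0.16 SD (ρ = 0.6), roughly 55% to 82% of it.

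**The case against.** The strongest reply is that a named test does not define an analysis set. The same t or rank tests can be run on imputed data, and the article neither states nor excludes this. Missing-data handling is commonly left to a fuller document, which is not shown. A reader might infer that the plan deletes every child without a record at a visit; the text does not say so, and its silence is not a fault. What stands is narrower. The article does fix the method for the primary comparison, that method has no longitudinal element, and a better use of records already collected is available.

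A reader might also infer that loss will favour the intervention. Nothing in the article forecasts this. Most sessions are delivered to whole classes, the same researcher collects data in both arms, and closer contact could raise record return in the intervention arm. Outcome-related loss alone is not enough: it must differ between arms.

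Nor does the article plan for 20% of 206, or 41 children, to be lost. The 20% is applied to 172.

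Finally, the calculation in step 4 suits the remedy, because loss there depends on a record that is always observed. Step 7 shows how much less is gained otherwise. This objection stands and limits the claim.

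**Conclusion.** The point holds as a conditional weakness of a stated analysis choice. On observed records, the visit-wise tests discard partial follow-up in a trial that itself allows for 16.5% loss. Where loss is tied to T1 intake in one arm, the T2 comparison shifts by about 0.03 to 0.13 SD at that loss and 0.04 to 0.16 SD at 20%. These sizes rest on assumed slopes, correlations and one-arm loss. The true size and sign are unknown, and the bias is zero under random loss or loss that is alike in both arms. The material does not show that the trial's result will be biased. It shows that the chosen tests leave avoidable exposure to bias, which merits a change of wording rather than a change of design.

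**What to change.** In Statistical analysis, replace the separate tests of intake with wording such as: *Fruit and vegetable intake will be analysed by one repeated-measures linear mixed model of all available T0, T1, T2 and T3 records from every randomised child, with arm, visit and arm-by-visit terms, child and classroom effects, and small-sample degrees of freedom. The effects at T2 and T3 will be estimated from the arm-by-visit contrasts. Record return will be reported by arm and visit.*

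Add one simple sensitivity analysis in which the assumed intake of non-returners in the intervention arm is lowered, for example by 0.25 and 0.5 SD. The classroom term and the degrees-of-freedom correction address clustering rather than loss. They belong in the model because there are only eight classrooms.

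The cost is wording and a little programming; the stated software fits such models and no new data are needed. The model relies on loss being explained by observed records. That is a weaker demand than the one made by the tests on available records, but not one the data can confirm, which is why the sensitivity analysis is needed. The rank-test fallback has no direct counterpart, so residuals should be checked.

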**Methods:**

Eligible classrooms within schools from Vitoria-Gasteiz (Basque Country, Spain) will be randomly assigned to the intervention (classrooms *n* = 4; children *n* = 86) or control (classrooms *n* = 4; children *n* = 86) group. The intervention group will receive 14 sessions of 60 min during an academic year (October to June). These sessions, designed by a multidisciplinary team, are based on TPB and are directed at modifying determinants of behavior (attitudes, subjective norms, perceived behavioral control and intention of consumption), and intake of FV itself. Both the process and the evolution of consumption and determinants of behavior will be evaluated (before, during, shortly after and a year after) using validated surveys, 7 day food records, 24 h reminders and questionnaires.

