## Methods

### Design

A cluster randomized controlled trial will be carried out over an academic year at school level. Classrooms from different schools and schools themselves will be the clusters of the study. Clustering was chosen because this is the easiest way to implement an intervention program at school level. In this way the phenomenon of contamination between children from the same classrooms is avoided.

Whole classes (a minimum of 26 children per classroom) from different schools will be part of the intervention or control group. The control group allows us to analyze the direct effect of the intervention and to discard an increase of FV intake by seasonality (first measurements will be in October and final ones in June) or other factors. The study was approved by the Ethic Committee of the University of the Basque Country (CEISH/262/2014/[name]) and all parents or legal guardians and school directors and teachers will be sent an informed consent before the study starts. Written informed consents will be sent to parents or legal guardians through the children. After having received consents, the collection of the first data will be carried out followed by the randomized allocation of classrooms.

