### Randomization and blinding

After baseline data collection, eligible classrooms from different schools will be randomly assigned to the intervention or the control group, by a random sequence generated using IBM-SPSS Statistical software. The personnel responsible for randomizing will be blinded to participants. Schools (directors, teachers and children) and families also will be blinded to their intervention or control group.

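### Classrooms are randomised (4 v 4), but fruit and vegetable intake is to be compared with tests that treat children as independent, so the 5% error rate does not hold

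*Protocol article*

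**What the plan says.** The Design section is explicit about the design: "A cluster randomized controlled trial will be carried out over an academic year at school level". It also names the clusters: "Classrooms from different schools and schools themselves will be the clusters of the study". Randomization and blinding makes the classroom the unit of allocation: "eligible classrooms from different schools will be randomly assigned to the intervention or the control group". The abstract gives the numbers: classrooms "will be randomly assigned to the intervention (classrooms *n* = 4; children *n* = 86) or control (classrooms *n* = 4; children *n* = 86) group".

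The Statistical analysis section then fixes the tests for the primary outcome, fruit and vegetable (FV) intake: "Intra-group and inter-group FV intake differences at T0, T1, T2 and T3, will be analyzed by" Student's t test or non-parametric alternatives (Wilcoxon signed-rank, Mann-Whitney U). It applies the same tests to the behavioural determinants. Multiple linear regression and structural equation modelling (SEM) follow for the secondary questions. Nowhere does the article mention a mixed model, generalised estimating equations (GEE), cluster-robust variance, a classroom-level summary or an ICC.

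The Sample size section counts children: "In order to provide a power of 90% to detect an effect size" (labelled Cohen's d) "of at least 0.5 servings/day, 172 participants (86 in the intervention group and 86 in the control group) are required". Recruitment is then set at "8 classrooms with a minimum of 26 children per class".

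**The concern.** Student's t and Mann-Whitney tests assume independent observations within each arm. Classmates are not independent here. They share a teacher, and in the intervention arm that teacher is trained to act as a model. They share the sessions and a poster of class intake that is meant to work through peer influence. The article itself chose clustering because classmates affect one another.

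With whole classrooms allocated, chance differences between classrooms enter the difference between arms. They do not bias its expected value, but they add error that a child-level standard error leaves out. That standard error is too small by the square root of the design effect. The test also uses 172 − 2 = 170 degrees of freedom, where 8 clusters support 8 − 2 = 6. P values come out too small and 95% confidence intervals too narrow. The Discussion would read an increase in intake as support for the programme as a valid tool, so a false positive would pass straight into the trial's conclusion.

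The within-arm tests (paired t, Wilcoxon signed-rank) have the same fault, because changes in children from one classroom are also correlated. The between-arm comparison matters most.

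**Working it through.** **Inputs.** From the article: 4 classrooms and 86 children per arm (abstract); power 90% and effect size 0.5 (Sample size); significance level 0.05 (Statistical analysis). Analysed children per classroom: m = 86/4 = 21.5. Assumed, because the article does not give them: a two-sided test, and ICC values of 0.01, 0.02, 0.05 and 0.10. The effect size carries the unit servings/day, and it equals a standardised 0.5 only if the SD is 1 serving/day.

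**Step 1: reproduce the plan's own figure.** For a two-sided t test on independent children at d = 0.5, the noncentral t distribution gives power 0.8999 at 85 per arm and 0.903 at 86. The smallest n reaching 90% is therefore 86 per arm, or 172 in total, exactly as stated. (A one-sided test would need 69 by the normal formula and does not match.) So the sample size assumes a design effect of 1 and the child as the unit.

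**Step 2: design effect.** DE = 1 + (m − 1) × ICC = 1 + 20.5 × ICC.

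**Step 3: true error rate of the child-level test.** The naive statistic has a standard deviation of about √DE under the null, so type I error ≈ 2 × [1 − Φ(1.96/√DE)].

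**Step 4: power of a valid test.** For a t test on classroom means with 6 df, the noncentrality is 0.5/√(2 × DE/86).

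| Assumed ICC | DE | √DE (factor by which SE is too small) | Type I error, formula | Type I error, simulated | Classroom-mean t test, simulated | Power of classroom-mean t test at d = 0.5 |
|---|---|---|---|---|---|---|
| 0.01 | 1.205 | 1.10 | 0.074 | 0.075 | 0.052 | 0.70 |
| 0.02 | 1.410 | 1.19 | 0.099 | 0.097 | 0.050 | 0.64 |
| 0.05 | 2.025 | 1.42 | 0.168 | 0.170 | 0.051 | 0.49 |
| 0.10 | 3.050 | 1.75 | 0.262 | 0.264 | 0.051 | 0.35 |

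The simulation used 20,000 runs per row, 4 v 4 classrooms of 21 children, and normal outcomes. With ICC = 0 the child-level test gave 0.052, as it should.

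**Step 5: sensitivity.**
- With all 26 children per classroom analysed, the formula gives 0.080, 0.110, 0.191 and 0.295, so larger classes make the inflation worse.
- The non-parametric option does not help. A separate simulation (5,000 runs) of the Mann-Whitney test gave 7.2%, 10.2%, 16.5% and 25.4%.
- Even at ICC = 0, the classroom-mean test has power 0.78, because it has only 6 degrees of freedom.

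**The case against.** **The unit of analysis is not stated.** A Student's t test on 8 classroom means is also a Student's t test and would be valid. The child-level reading is an inference. It is a strong one: the sample size reproduces exactly as a child-level calculation, the arms are described as 86 v 86 participants, and no classroom summary is mentioned anywhere.

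**The article is condensed, and an analysis plan may exist.** That would answer a silence, but this section names the tests. A later plan could put the matter right only by departing from the published text. The argument does carry weight for the regressions and SEM: classroom terms or robust errors are compatible with what is written, and those models serve secondary objectives. They are covered below only as a consequence of the main correction.

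**The ICC is unknown and may be small.** Parents complete the 7-day record and much eating happens at home, so variation between households may dominate. This stands. The article cannot place the trial within the range of 7% to 26%, and the upper figure should not be read as the expected one. The direction, however, holds for any positive ICC, and at 0.01 the error rate is already about 7%.

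**A valid analysis loses power.** This is true and has to be disclosed. It is no reason to keep a test whose error rate is not controlled.

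**Conclusion.** The concern holds and must be fixed before the primary result is interpreted. The design randomises classrooms, and the tests named for the primary outcome, read with the sample size section, are child-level tests that ignore this. At a nominal 5%, the true two-sided type I error is about 7%, 10%, 17% and 26% for ICC 0.01, 0.02, 0.05 and 0.10, and the child-level standard error is too small by a factor of 1.10 to 1.75.

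These sizes rest on the assumed ICC range, 21.5 analysed children in each classroom, and independent classrooms. The Design section also names schools as clusters. If two classrooms of one school fall in the same arm, shared school influences add correlation that these figures do not include.

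**What to change.** **Between-arm tests of intake.** Replace them with a linear mixed model for FV intake with a random intercept for classroom and small-sample degrees of freedom. Keep the intercept even if its variance is estimated as zero. A t test on the 8 classroom means with 6 degrees of freedom is an acceptable alternative. If a non-parametric option is wanted, permute arms over classrooms. With unrestricted 4 v 4 allocation there are 70 arrangements, so the smallest two-sided p value is 2/70 = 0.029.

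**Schools.** State whether any school supplies more than one classroom. If so, account for school in whichever option is chosen; the classroom-mean t test on 6 degrees of freedom is then no longer sufficient by itself.

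**Other analyses.** Carry the same clustering into the within-arm changes, the determinants and the regressions. For the SEM, use cluster-robust standard errors or label the results as descriptive. Report the ICC for intake.

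**Cost.** No new data are needed: allocation was by classroom, so each child's classroom is known, and STATA is already listed. Confidence intervals will be wider. The stated 90% power no longer applies: the classroom-level test has 0.70, 0.64, 0.49 and 0.35 at d = 0.5 for the four ICC values. The amended text should say so. Adjusting for T0 intake, which is already collected, may recover some precision, but the article gives no figure from which to say how much.

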### Study procedure

The intervention program will last one academic year. After randomization, meetings will be held with teachers of each classroom to describe the specific program to be carried out by each classroom without telling them which group they belong to (control or intervention) and to set the dates of sessions and evaluation procedures. Teachers of the intervention groups will receive some training, as they are models for children. All intervention and control sessions will be held by the same nutritionist, and data collection at baseline (T0: September), during (T1: January) and after (T2: June) intervention will be performed by the same researcher. To check any long-term effect, the measurements will be carried out one year after the end of the intervention (T3: June). Diagram of the study timeline is presented in Fig. 1

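### FV intake is recorded before randomisation, but the arms are compared with unadjusted tests at each visit, which loses precision and leaves any chance imbalance between 4 and 4 classrooms in the realised result

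*Protocol article*

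**What the plan says.** The primary outcome is FV intake in servings from a 7-day record (Outcomes, primary outcome). Study procedure places "data collection at baseline (T0: September), during (T1: January) and after (T2: June) intervention", with a further measurement one year later (T3). Randomization and blinding states that "After baseline data collection, eligible classrooms from different schools will be randomly assigned" to the arms, so T0 intake is measured before allocation. The Abstract gives four classrooms and 86 children in each arm.

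Statistical analysis fixes the arm comparison: "inter-group FV intake differences at T0, T1, T2 and T3, will be analyzed by" Student's t test or a rank test. The same sentence covers within-arm differences, and the same tests are planned for the determinant scores. For baseline, the section plans to "describe baseline characteristics of intervention and control group to assure comparability between groups". The regression closest to the treatment effect serves a different aim: "Multiple linear regression will be used to study the effect of social demographic variables in the effectiveness of the intervention". Baseline intake is not named as a covariate in any comparison of the arms.

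**The concern.** A measurement of the outcome taken before randomisation is usually the most useful covariate a trial has. Here it is available and is left out of the comparison that answers the main objective.

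The T0 between-arm test does not replace it. After random allocation, that test only asks whether chance produced a difference that is known to be due to chance. A non-significant result does not show that the arms are comparable, and a significant one corrects nothing.

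With eight randomised units, chance imbalance can be material, and a raw comparison at T2 carries part of it into the estimate. Precision is also scarce in a trial of this size, and baseline adjustment is a cheap way to recover some.

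**Working it through.** **Inputs from the protocol article.** 4 classrooms and 86 children per arm (Abstract), so 86/4 = 21.5 children per class. At least 26 children per class at enrolment (Design; Sample size). Target effect 0.5, power 90% (Sample size), significance level 0.05 (Statistical analysis). The target is called Cohen's d but given in servings/day; it is taken here as 0.5 SD.

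**Assumed, because the document gives neither.** ICC 0.02 to 0.05; correlation r between T0 and follow-up intake of 0.3, 0.5 or 0.7.

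**1. The plan's own sample size.** Two-sided normal approximation: n per arm = 2 × (1.960 + 1.282)² / 0.5² ≈ 84.1, rounded up to 85. With the noncentral t, power is 89.99% at 85 and 90.3% at 86 per arm. The stated 86 is therefore that of an unadjusted two-sample t test on independent children. The sizing and the planned test agree with each other, and neither uses T0.

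**2. Size of chance imbalance at T0.** For 4 classes of m children per arm, in SD units:

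SD of the difference in baseline means = √{2 × [ICC + (1 − ICC)/m] / 4}

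| m | ICC | SD of difference | P(gap above 0.25 SD, either direction) |
|---|---|---|---|
| 21.5 | 0.02 | √(0.5 × 0.0656) = 0.181 | 0.167 |
| 21.5 | 0.05 | √(0.5 × 0.0942) = 0.217 | 0.249 |
| 26 | 0.02 | √(0.5 × 0.0577) = 0.170 | 0.14 |
| 26 | 0.05 | √(0.5 × 0.0865) = 0.208 | 0.23 |

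**3. What a gap does to the raw follow-up comparison.** Expected shift = r × gap, assuming equal SDs at both times and the same r at child and classroom level. At r = 0.5 and a gap of 0.25 SD this is 0.125 SD, and 0.125/0.5 = 25% of the target effect.

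**4. Child-level gain from adjustment.** The residual variance factor is 1 − r². For a change score it is 2 − 2r, which is never smaller, because (2 − 2r) − (1 − r²) = (1 − r)² ≥ 0.

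| r | Adjusted: 1 − r² | Reduction | Change score: 2 − 2r |
|---|---|---|---|
| 0.3 | 0.91 | 9% | 1.4 |
| 0.5 | 0.75 | 25% | 1.0 |
| 0.7 | 0.51 | 49% | 0.6 |

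**5. Gain at trial level.** Simulation used 6,000 runs, 4 + 4 classes of 22, ICC 0.05, effect 0.5 SD, the same r at both levels, and a classroom-level t test on 6 degrees of freedom. Power was about 49% unadjusted and 53%, 60% or 77% adjusted for r = 0.3, 0.5 or 0.7.

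**6. What adjustment does not do.** In the same simulations with no effect, tests that treat children as independent rejected in about 10%, 17% and 27% of runs at ICC 0.02, 0.05 and 0.10. The rates were practically the same with and without T0 adjustment.

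**The case against.** The strongest reply is that this concerns efficiency, not validity. Randomisation makes the unadjusted comparison unbiased over repeated allocations, and a correctly computed standard error already allows for chance imbalance. The sample size was also derived for an unadjusted test. All of this stands, and it limits the point to precision and the one realised result.

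A second reply is that covariates are commonly left to an analysis plan. It carries less weight here, because the article itself names the between-arm tests.

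A third is that the differences to be tested might be change scores. The wording, which lists T0 among the visits at which they are analysed, points to a comparison at each visit. Change scores would in any case be no more precise than adjustment.

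Four stronger readings are tempting, and the document does not support them:

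- *A sizeable imbalance is likely.* Under the assumptions above, 75% to 83% of allocations stay within 0.25 SD with 21.5 children per class. An imbalance of that size is a real possibility, no more.
- *Allocation was not balanced.* The article mentions a software-generated random sequence and is silent on stratification or blocking. Silence in a condensed article does not show that there was none. If balancing was used, the probabilities above could be lower.
- *T0 is used only for description and a T0 test.* The within-arm paired tests use it too. They do not adjust the arm comparison.
- *The percentage reductions in child-level variance are the trial's gain.* With four classes per arm, the gain also depends on the classroom-level correlation, which is unknown.

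**Conclusion.** The point holds as a matter of efficiency and should be acted on; it does not by itself invalidate the trial. The article fixes an unadjusted comparison of the primary outcome although a valid pre-randomisation measurement of it exists, and the T0 between-arm test is no safeguard.

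The reading of the text is secure. The size is conditional: the imbalance probabilities rest on the assumed ICC, the shift and variance reductions on the assumed correlation, and the trial-level power on both. At r = 0.3 the gain is small (about 49% to 53% power at ICC 0.05); at r = 0.7 it is large (about 49% to 77%).

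A reader might infer that baseline adjustment would make the planned tests sound. It would not. Ignoring classroom clustering is a separate and larger problem, and adjustment alone leaves it in place.

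**What to change.** Replace the between-arm tests with an ANCOVA-type comparison of follow-up servings/day, adjusted for the child's T0 servings/day. Name T2, the end of the intervention, as the primary time point. Account for classroom either by a mixed model with a classroom random effect and a small-sample degrees-of-freedom correction, or by a two-stage classroom-level analysis. Drop the T0 between-arm significance test and keep the baseline table as description. Treat the determinant scores the same way.

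The classroom T0 mean may be added as a covariate. It uses one of about 6 degrees of freedom and raises the critical t from 2.45 to 2.57, so it is optional.

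Cost: no new data. Because the article reports the study as ongoing, the change needs a dated analysis amendment made before outcomes by arm are examined. It also needs a stated rule for children without a T0 record.
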